### Data collection and research strategy summary

After the development of the scoring system, we will prospectively collect data in a variety of settings, with clinicians (*n* = 120) who have varying levels of experience and expertise with CBT. We will collect data on clinician, client, and organizational characteristics that may impact the assessment of psychotherapy quality. We will collect worksheets, symptom measures, clinical notes with checklists of CBT strategies embedded within them, and therapy session recordings for participating clients. They will be provided to the investigators using secure, Institutional Review Board (IRB)-approved modes of data transmission that have been used successfully in our previous research [44–47].

Participating clients will be randomized into one of two different worksheet formats—app version or paper form (content is the same, mode of completion and data transmission differs). Raters will access the copies of the worksheets, or the mobile app dashboard, and score the worksheets. Clinicians, administrators, supervisors, and clients will be interviewed to assess perceptions of the quality assessment strategies and to determine feasibility, and these data will be analyzed using qualitative strategies.

The variety of worksheets and data capture sources (apps, paper forms) will allow assessment of clinician and client preferences, the degree of detail and completion required for accurate quality assessment. This strategy will allow us to answer several questions through our statistical and qualitative analyses. Analyses will be conducted to answer questions and test hypotheses regarding (1) the reliability and factor structure of the measure, (2) associations between the quality measure and subsequent symptom change (the primary outcome), (3) the concurrent validity of the measure, (4) whether the measure performs better than adherence checklists embedded in clinical notes, (5) whether different formats (apps vs. paper forms) have different concurrent or predictive validity, and (6) the feasibility, burden, satisfaction, and time requirements for the worksheets vs. the adherence checklists.

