#### Worksheet transmission

Clinicians will redact any potential identifiers from worksheets and indicate whether they were completed/reviewed in session or for homework. Paper worksheets will be transmitted by fax or scanned and transmitted electronically (e.g., secure email, shared network drives, and HIPAA-compliant data storage software) depending on local capacity and regulations. The mobile apps will record the scheduled session time and timestamp the worksheets to allow discernment of whether worksheets were done in session. We will use Qualtrics to develop app-based standard cognitive and behavioral worksheets used for depression, anxiety, and PTSD. We will only score worksheets that are done in session to measure quality; scoring of worksheets that are completed for homework will be used to covary client skill in analyses.

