#### Clinical outcome predictions

We expect that clients whose sessions receive higher quality ratings will exhibit larger decreases in symptoms compared to clients whose sessions had lower ratings. Based on previous research suggesting that it is important to assess fidelity in early sessions to avoid temporal confounds between process variables and outcomes [22, 68, 74, 75], we expect that quality in earlier sessions will more accurately reflect the contributions of session quality and clinician skill (rather than client factors) than that in later sessions. Primary analyses will focus on quality in sessions 1–6. We will cross-validate prediction models as a way of checking internal validity (generalization error).

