The next multi-level regression analyses will examine the session-by-session associations between quality and symptoms. Lagged multivariate models will allow for the inclusion of two outcomes (quality and symptom change) in the same model [78–80]. Evaluation of the cross-lagged paths will provide information about temporal precedence in the relationship between the two variables across time. We will also account for overall increases and decreases in the model by including time as a predictor of each outcome.

We will next determine whether the different quality measures or worksheet formats differ in terms of how strongly they are associated with subsequent symptom change. Since clients will be randomized into worksheet format (app vs paper form), a dichotomous variable with paper form as the reference will be entered at Level-2 in the analyses described above to examine whether format predicts symptom change. We will explore potential interactions with target problem (PTSD, depression, anxiety). We will examine and compare the effect sizes and the proportion of variance accounted for by the worksheet measure and the adherence checklist. We will also compare them for app vs. paper form worksheets. A medium or large effect would be clinically meaningful in the context of the pragmatic goals of this project, particularly because the reliable change index for each of our outcome measures corresponds to a large effect size [48, 49, 58]. On the other hand, if associations with outcomes differ only slightly, we would recommend selection of a quality assessment strategy based on specific programs’ needs or goals.

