#### Comparisons of quality measures (worksheet vs. adherence checklists) and worksheet formats

If self-reported adherence (as assessed through the checklists embedded in clinical notes) is highly correlated with worksheets and/or the gold standard observer ratings, and if they are strongly associated with outcomes, the checklists alone may be deemed sufficient for quality assessment, because the notes can already be accessed by quality monitors in each system. First, we will use the Fisher *r*-to-*z* transformation to calculate a value of *z* that can be applied to assess the significance of the difference between two correlation coefficients. This analysis is conducted to assess whether a significant difference exists between correlations with the gold standard observer ratings. If there is no significant difference, this would indicate that the worksheet quality scoring strategy does not yield an advantage or disadvantage in terms of its correspondence with gold standard observer ratings. We will also use this strategy to determine whether a difference exists between correlations with worksheet formats (app vs. traditional paper form) and observer ratings [48].

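### The worksheet-checklist comparison on symptom change has no test or interval for the difference, and its rule for slight differences has no number

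*Protocol article*

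**What the plan says.** In the Protocol article, Data collection and research strategy summary, the fourth listed question is "whether the measure performs better than adherence checklists embedded in clinical notes". The Analyses section takes this up for symptom change: "We will next determine whether the different quality measures or worksheet formats differ in terms of how strongly they are associated with subsequent symptom change". The method for the two measures is: "We will examine and compare the effect sizes and the proportion of variance accounted for by the worksheet measure and the adherence checklist".

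Two sentences then guide interpretation. One reads "A medium or large effect would be clinically meaningful in the context of the pragmatic goals of this project". It does not say whether the effect is one measure's association with outcome or the difference between measures. The other says that "if associations with outcomes differ only slightly, we would recommend selection of a quality assessment strategy based on specific" requirements of each program. No number defines a slight difference.

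The section Comparisons of quality measures (worksheet vs. adherence checklists) and worksheet formats names the Fisher r-to-z transformation and limits its scope: "This analysis is conducted to assess whether a significant difference exists between correlations with the gold standard observer ratings".

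On which sessions carry a score, Worksheet transmission states "We will only score worksheets that are done in session to measure quality". Raters and scoring takes the checklist score from the clinical note. Both materials are to be collected for participating clients.

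**The concern.** Predictive validity is what the study is powered on, but that power is for one association. The comparison of two associations, which feeds the advice to services, is given a descriptive method only.

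Without an interval for the difference, two errors are possible. A visible gap between equally good measures may be read as real. A small observed gap may be read as near-equality when the data are too imprecise to show it, so that a real difference is dismissed as slight. With no number for slight, the reading of a given result is open until the result is known.

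**Working it through.** **Inputs from the Protocol article.** 360 clients (Client inclusion criteria). Six observations per client, design effect up to 2.04, 37% attrition and missing data, two-tailed alpha .05, r = .30, power above .80 (Sample size justification and power calculations).

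**Assumptions.** The worksheet-checklist correlation r12 is not given; .1 to .7 is used. The effective n is not fixed by the text, so several readings are shown.

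**Step 1: the plan's own figure.** For one correlation, the n needed is ((1.96 + 0.84)/atanh(.30))² + 3 = 85, or 173 after multiplying by 2.04. Power is Φ(atanh(.30)·√(n − 3) − 1.96):

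- n = 360 × 0.63 = 227: .996
- n = 360/2.04 = 176: .983
- n = 227/2.04 = 111: .896

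The stated power above .80 reproduces on every reading. It says nothing about a difference between two associations.

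**Step 2: precision of the difference.** For two correlations r1 and r2 with the same outcome, in the same records:

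- ψ = r12(1 − r1² − r2²) − ½·r1·r2·(1 − r1² − r2² − r12²)
- c = ψ/[(1 − r1²)(1 − r2²)]
- SE(z1 − z2) = √[(2 − 2c)/(n − 3)]

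Example: r1 = r2 = .30, r12 = .1, n = 227. ψ = .1 × .82 − .045 × .81 = .0456. c = .0456/.8281 = .055. SE = √(1.89/224) = .092, and the 95% half-width is 1.96 × .092 = .18. The chance of a gap above .10 when the measures are equal is 2[1 − Φ(.10/.092)] = 28%.

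Ranges below run over r12 from .7 to .1. The last two columns take true values .30 and .20, a Fisher-z gap of .310 − .203 = .107.

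| n | Basis | 95% half-width | Gap > .10, equal measures | Power, .30 vs .20 | Wrong order, .30 vs .20 |
|---|---|---|---|---|---|
| 227 | 360 × 0.63 | .11-.18 | 6-28% | 22-52% | 2-12% |
| 360 | all clients | .08-.14 | 2-17% | 32-72% | 0.6-7% |
| 667 | 227 × 6/2.04 | .06-.105 | 0.1-6% | 52-93% | 0.03-2% |
| 1059 | 360 × 6/2.04 | .05-.08 | under 2% | 72-99% | under 1% |

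At n = 111 the chance of a gap above .10 is 20-45%. That is a floor only: 2.04 already allows for repeated observations within a client, so dividing clients by it counts that correlation twice.

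**Step 3: simulation check** (5,000 draws per setting, n = 227, equal measures, r12 = .7 and .3). The SD of r1 − r2 was .049 and .073. Step 2 gives .054 × .91 = .049 and .081 × .91 = .074, where .91 = 1 − .30² converts z to r. The two agree.

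**Step 4: proportion of variance**, the plan's second yardstick, taken as simple r² in the same draws. With equal measures, one exceeded the other more than 1.5-fold in 23-41% of draws at n = 227 and in 1-7% at n = 1059.

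**The case against.** The strongest reply is that the plan does not let chance choose. A reader might infer that any numerical lead picks the winner; the sentence on slight differences rules that out, and this part of the reply stands. If the bar is a medium difference (taken here as a Fisher-z gap of about .30), equal measures cross it by chance in at most 0.1% of trials at n = 227. If session-level information counts in full, gaps above .10 occur in under 2%. Both points stand as arithmetic. But the text does not say that the bar applies to the difference, and it does not settle the level at which quality acts.

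The recommendation also does not rest on this comparison alone. Checklists may suffice if they correlate highly with worksheets or observer ratings and are strongly associated with outcomes, and the observer-rating comparison has a named test. That limits the consequence. The planned cross-validation of prediction models is not tied to this comparison.

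An article may leave intervals to the analysis plan, and comparing effect sizes does not exclude one. However, the article states a method for this question, and that method is descriptive, while the next section names a test for the parallel question.

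A reader might also infer that the two measures will be compared on different sets of sessions, because worksheet scores need an in-session sheet. The documents do not support that: both materials are planned for the same clients, and the article does not state which sessions enter. Treating the 120 clinicians as the unit would make the chance gaps look larger, but the plan has no such analysis and gives a clinician-level ICC of .01.

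**Conclusion.** The point holds in a limited form. The comparison of worksheet and checklist on subsequent symptom change has no test or interval for the difference, and the rule for slight differences has no number. An observed gap therefore cannot be told from sampling error, and near-equality cannot be told from imprecision.

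The size depends on the effective n. At client level the problem is material: at n = 227 the 95% half-width is .11-.18 in Fisher z, and chance gaps above .10 occur in 6-28% of trials. At n of about 1059 it is small. These figures rest on true correlations of .30, an assumed between-measure correlation of .1-.7, and a .10 threshold chosen here for illustration. The documents do not support the stronger claim that noise will pick the winner. The stated power for the primary association is not in question.

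**What to change.** In Analyses, replace the descriptive comparison with an estimate of the difference between the two standardised associations on sessions that have both scores. Use either both measures in the same growth or lagged model, or paired models. State which, because the scales differ: with two standardised predictors alone, b1 − b2 = (r1 − r2)/(1 − r12).

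Report the difference with a 95% interval from a bootstrap that resamples clinicians. Put a number on a slight difference, on the chosen scale, and say whether the sentence about a medium or large effect refers to an association or to the difference. Then base the recommendation on the interval:

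- wholly within the margin: the difference is slight, and programs choose;
- wholly beyond the margin: one measure is preferred;
- otherwise: inconclusive.

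Set the margin with the attainable precision in mind. At n = 227 the half-width exceeds .10 throughout the assumed range, so a margin of .10 in Fisher z could not be met even with an observed difference of zero.

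Show each measure on all its own sessions as a secondary analysis. The added value of each measure over the other is optional. The cost is plan wording and a bootstrap, with no new data. The small downside is that the main comparison uses only sessions with both scores.

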#### Sample size justification and power calculations

In light of the project’s emphasis on the development of pragmatic measurement strategies that predict changes in the target problems, we powered the study to test for predictive validity. Calculations of a design effect (measure of how the design effects the standard error of the parameters) [81, 82] accounted for clustering. We computed ICC with repeated observations of clients at the clinic (*r*_*pb*_ = .01), clinician (*r*_*pb*_ = .01), and client (*r*_*pb*_ = .10) level in our prior research, assuming three clients per clinician, and six clinicians per cluster, and six observations per client, yielding a design effect of up to 2.04. We based the estimated number of observations per client to conservatively account for potential 37% client-level attrition and missing data during the treatment. For the growth curve analyses to assess whether the quality measure predicts symptom change (our primary analysis), the probability of a type 1 error (alpha) at two-tailed .05 power exceeds .80 for an effect size of *r* = .30, which corresponds with small-to-medium effects of fidelity on symptoms in prior CBT fidelity research [68, 83]. We also projected a sample size to be sufficient to conduct separate analyses and test for interactions with disorder (PTSD vs. depression vs. anxiety), app vs. paper form, and other variables of interest, and detect an effect size of .50, a medium effect.

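### The tie rule for recommending a quality measure or worksheet format sets no minimum association with symptom change, so two options that predict nothing also count as a tie

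*Protocol article*

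**What the plan says.** The protocol article treats the association between the quality measure and later symptom change as its primary outcome (Data collection and research strategy summary) and powers the study on it: "power exceeds .80 for an effect size of *r* = .30" (Sample size justification and power calculations).

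After the predictive models, the Analyses section turns to comparison: "We will examine and compare the effect sizes and the proportion of variance accounted for by the worksheet measure and the adherence checklist". The same comparison is planned for app versus paper. Two sentences then interpret the result. The first is a benchmark: "A medium or large effect would be clinically meaningful in the context of the pragmatic goals of this project", supported by the reliable change index of the symptom scales. The second, introduced as a contrast, is the rule at issue: "if associations with outcomes differ only slightly, we would recommend selection of a quality assessment strategy based on specific programs’ needs or goals".

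The next section, Comparisons of quality measures, adds a condition for one option. If the checklists correlate highly with worksheets and/or observer ratings, and "if they are strongly associated with outcomes, the checklists alone may be deemed sufficient for quality assessment".

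**The concern.** The tie rule depends on one quantity, the gap between two associations. It does not ask whether either association exists. Two null associations have a small gap, so they take the same branch as two equally good predictors. There is no branch for the case in which neither option predicts symptom change, and nothing connects the result of the primary analysis to the recommendation.

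The null case is realistic here. The Background section itself reports a meta-analysis with no overall link between observer-rated fidelity and symptom change. Which strategy programmes should adopt is the study's practical conclusion. A study whose worksheet score failed its primary test could still end by advising programmes to pick a strategy to suit their needs, which readers would take as support for both options.

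**Working it through.** **Inputs from the protocol article.** 360 clients; six observations per client; design effect up to 2.04; 37% attrition and missing data; two-sided alpha .05; planned r = .30.

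**Assumptions.** 1:1 allocation to formats (the ratio is not stated), so 180 per arm. Correlation of .3 between worksheet and checklist scores. *Slightly* has no cut-off, so two are tried on the Fisher z scale, with q = atanh(r1) − atanh(r2): |q| < .10 and |q| < .30. The multilevel association is represented by a simple correlation.

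**The plan's own power statement.** Power = Φ(atanh(.30)·√(n − 3) − 1.96), with atanh(.30) = .3095.
- n = 360 × 6 / 2.04 = 1059: power > .999
- n = 360 / 2.04 = 176: power .983
- n = 360 × .63 / 2.04 = 111: power .896. This is a pessimistic bound, because the article already builds the 37% into the six observations per client.

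The stated power above .80 is reproduced in every case.

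**Worksheet versus checklist, both true r = 0, N = 360.** The two correlations share the outcome, so SD(q) ≈ √[2(1 − .3)/(360 − 3)] = .0626.
- |q| < .10: 2Φ(.10/.0626) − 1 = .89
- |q| < .30: 2Φ(.30/.0626) − 1 = 1.00

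A simulation of 20,000 trials gave .89 and 1.00.

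**App versus paper, both true r = 0.** The arms are independent, so SD(q) = √[2/(n per arm − 3)].

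| n per arm | SD(q) | P(abs q < .10) | P(abs q < .30) |
|---|---|---|---|
| 180 | .106 | .65 | .995 |
| 88 (176/2) | .153 | .49 | .95 |
| 56 (111/2) | .195 | .39 | .88 |

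**Does the branch separate useless options from useful ones?** With both true r = .30 at N = 360, worksheet versus checklist fires in .88 (|q| < .10) and 1.00 (|q| < .30) of simulated trials. These are practically the null-case figures (.89 and 1.00).

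**Effect of a floor.** Require an option's own two-sided 95% interval to lie above 0, with the expected direction taken as positive. Under the null each option passes with probability .025, so the chance that at least one of two passes is at most 2 × .025 = .05. In simulation at N = 360, the chance of a tie with at least one measure passing was .026 (|q| < .10) to .045 (|q| < .30). With both true r = .30 the floor lost nothing at N = 360 for the two measures (.88 and 1.00, with both passing).

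For formats the floor costs more as the arms shrink. Each arm's chance of passing at r = .30 is Φ(.3095·√(n − 3) − 1.96): .98 at 180, .82 at 88 and .61 at 56 per arm.

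**The case against.** **The article does contain a floor.** The condition that the checklist be strongly associated with outcomes is a real safeguard, and it covers the option most likely to be chosen for convenience. But it governs only acceptance of the checklist alone. It does not cover the worksheet score, either format, or the tie branch.

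**The benchmark may be a floor.** The sentence calling a medium or large effect meaningful could refer to a single association rather than to a difference, and its appeal to the reliable change index fits that reading at least as well. The text does not settle this. A charge that the benchmark is on the wrong scale would therefore depend on one reading of an ambiguous sentence. Even on the kinder reading, the tie branch is not made conditional on the benchmark.

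**This is narrative, and details belong in the analysis plan.** Exact cut-offs may well be left there. But the article prints the trigger and its consequence, and that logic is incomplete whatever the cut-off.

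**A stronger reading is tempting.** A reader might infer that a checklist with a third of the worksheet's association (r = .10 against .30) would be treated as interchangeable with it. At N = 360 that pair falls within |q| < .30 in about 92% to 93% of simulated trials, but within |q| < .10 in only about 4%. The document does not say that *slightly* means anything below medium, so this inference is not supported.

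**Conclusion.** The tie branch is wrong as written because it lacks a minimum association. This follows from the text and needs no simulation. The numbers show how often it would matter if both true associations were 0: 89% to 100% of trials for worksheet versus checklist at 360 clients, and about 65% to nearly 100% for app versus paper at 180 per arm.

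A reader might infer that the branch fires almost every time under the null. That holds for the two measures at this sample size, but not for formats under a strict cut-off, where the rate is about 40% to 50% at effective arm sizes of 56 to 88.

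The figures rest on the assumed inter-measure correlation, the assumed cut-offs and 1:1 allocation. The conclusion that the branch cannot tell two null options from two useful ones does not.

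**What to change.** In the Analyses section:

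1. Apply the programme-needs branch only among measures or formats whose own association with subsequent symptom change has a two-sided 95% confidence interval excluding 0 in the expected direction. If none qualifies, state that no strategy is recommended on predictive validity.
2. Report the difference between associations with its 95% confidence interval.
3. Say whether the medium-or-large benchmark refers to an association or to a difference between associations.

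The fallback should not be a default to observer rating. The Background section calls observation infeasible in many practice settings and reports no overall link between observer-rated fidelity and symptom change.

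The cost is a few sentences and no new data. The study may end with no recommended strategy. For formats, a useful option could miss the floor if the effective sample per arm is small.
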